### Criteria for discontinuing or modifying allocated interventions {11b}

This study has a single time-point intervention, making discontinuation of the intervention during follow-up a non-relevant issue. When a participant in the intervention group does not undergo the [^18^F]FET PET scan, this can be due to worsened clinical condition (or death) or participant request.

### Strategies to improve adherence to interventions {11c}

As the intervention is a single [^18^F]FET PET scan that is performed almost directly after randomization, no specific monitoring adherence procedures are applicable.

### Relevant concomitant care permitted or prohibited during the trial {11d}

Standard-of-care follow-up with MRI scans and standard-of-care diagnostic procedures and treatments such as biopsy, debulking, chemotherapy, reirradiation, and supportive therapies (e.g., bevacizumab, dexamethasone) are allowed in this trial. There is no prohibited concomitant care in this trial.

### Provisions for post-trial care {30}

As [^18^F]FET PET is a well-established, safe imaging method in glioma patients and is recommended in Dutch and international guidelines as a standard-of-care option, the risk of suffering harm from trial participation is considered negligible. Therefore, post-trial care provisions such as post-trial monitoring/visits are not applicable. Standard clinical follow-up of the participants will be performed by their treating physicians, ensuring sufficient care.

### Outcomes {12}

#### Primary study outcomes

##### Co-primary outcome 1

Undergoing any unnecessary intervention(s), as defined below. Determination of this dichotomous outcome measure “unnecessary interventions” will be done retrospectively, by the researchers and the treating physician after 6-month follow-up.

An “unnecessary intervention” is defined as:Biopsy or debulking for diagnostic uncertainty and/or with pseudoprogression as the final pathological diagnosis.The administration of one or more cycles of (temozolomide) chemotherapy as continued treatment for presumed pseudoprogression, in cases where the final diagnosis is tumor progression. The final diagnosis is based on clinicoradiological- and/or histopathological evidence.Starting and/or altering chemotherapy for presumed tumor progression, in cases where the final diagnosis is pseudoprogression. The administration of one or more doses of bevacizumab for presumed pseudoprogression, in cases with a final diagnosis of tumor progression.

##### Co-primary outcome 2

Health-related quality of life (HRQOL) (continuous measure): the European Organization for Research and Treatment of Cancer Quality of Life Core Questionnaire (EORTC-QLQ-C30) + Brain Cancer Module (EORTC-QLQ-BN20) at *t* = 12 weeks, preferably completed before follow-up imaging is performed.

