## Introduction

### Background and rationale {6a}

Glioblastomas are incurable progressive brain tumors with a variable, but poor prognosis. After surgery, chemoradiation with concomitant and adjuvant temozolomide chemotherapy offers effective, albeit temporary, palliation for many patients, with median overall survival of 14–16 months [1, 2]. In the months following radiotherapy, ~ 50% of patients will develop changes on MRI, suggestive of recurrence. In a majority of these patients, these MRI changes are classified as pseudoprogression [3]. Pseudoprogression is defined as treatment-induced increasing, or new, contrast enhancement which is mostly self-limiting and requires a different management strategy than tumor recurrence. Pseudoprogression will be used in this paper as an encompassing term that includes radionecrosis and other treatment-related effects after (chemo-)radiotherapy. Discrimination between pseudoprogression and tumor progression on MRI can be notoriously challenging [4]. In the patients that are eventually diagnosed with pseudoprogression, initial diagnostic uncertainty is common, which may lead to an increased risk of misdiagnoses and unnecessary interventions [5, 6].

Currently, in the Netherlands, in these patients with diagnostic uncertainty on MRI, the multidisciplinary team prefers to wait for a next scan in 6–12 weeks’ time for definitive diagnosis, leading to potential delay of diagnosis and adequate management and causing psychological burden for patients and their relatives with impact on quality of life [7].

The use of positron emission tomography (PET) with the radioligand [^18^F]Fluoro-ethyl-tyrosine, or [^18^F]FET PET in short, has the potential to differentiate treatment-related changes from tumor recurrence with higher accuracy compared to current clinical standard MRI including perfusion-weighted MRI [8–10]. Meta-analyses of literature confirm that addition of [^18^F]FET PET to MRI has higher diagnostic accuracy for differentiation of pseudoprogression from tumor recurrence compared with MRI alone [11, 12]. Recent literature has led to evidence-based recommendations by the Response Assessment in Neuro-Oncology (RANO) working group to add [^18^F]FET PET imaging to MRI in cases with diagnostic uncertainty [13].

However, this advice is not based on prospective randomized patient benefit- or cost-effectiveness studies, as neither have been performed.

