### Intervention description {11a}

Patients in the investigational arm will undergo the extra [^18^F]FET PET scan, with use of the O-(2-^18^F-fluoroethyl)-L-tyrosine ([^18^F] FET) tracer. The tracer will be provided free of charge by Curium™ for a subset of the patients (based on logistical availability and scheduling per patient). For this study, Curium™ does not have a role in the design, execution, analysis, interpretation, manuscript writing and/or decision to publish.

[^18^F]FET PET scanning will be performed according to the joint European Association of Nuclear Medicine (EANM)/European Association of Neurooncology (EANO)/Response Assessment in Neurooncology (RANO) guideline [20]. In most patients, a static scan (20–40 min post-injection) will be performed. Patients will be asked for additional (opt-in) consent to undergo a dynamic [^18^F]FET PET scan. If the logistics of the research site allow for this scan, these patients will undergo dynamic scanning (continuous scanning 0–40 min post-injection). Interpretation will be done by a nuclear medicine physician from the local center according to current European guidelines [20]. Central review will be performed by a panel of nuclear medicine physicians from the study team, specialized in [^18^F] FET PET scans.

Patients are treated according to current standard-of-care that is determined by the treating physician/multidisciplinary team, but will be based on the diagnosis from the static [^18^F]FET PET findings:In case of [^18^F]FET PET-diagnosis of tumor recurrence: a change in treatment regime will be made. Redo-debulking will be done only for clinical indications, including mass reduction or cytoreduction.In case of [^18^F]FET PET-diagnosis of pseudoprogression, or equivocal results: the ongoing treatment or observation will be continued, with addition of steroids and/or bevacizumab if needed for symptom relief. Redo-debulking will only be done for the rare indication of refractory symptoms of mass effect due to pseudoprogression.

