### Sample size {14}

From current practice (survey among the participating centers), we estimate that 37% of the glioblastoma patients that meet our inclusion criteria, eventually undergo unnecessary interventions (control arm). In the intervention arm, we expect this proportion to be much lower (~ 12% from clinical scenarios), due to the high accuracy of [^18^F]FET PET. Using a two-sided *Z* test with pooled variance with an alpha of 0.05, based on a power of 90%, we need 61 patients in each arm, so 122 in total. Due to the intention-to-treat set-up and unnecessary treatment as outcome measure, we expect that virtually all patients can be included in final analysis, with minimal drop-out. For the co-primary endpoint of HRQOL (EORTC-QLQ-C30 + BN20) at *t* = 12 weeks, drop-out due to missing questionnaire data is estimated at 10%. With addition of this drop-out rate, we will randomize 144 patients, 72 patients per study arm.

Methodologically, the two primary endpoints are hierarchical: the first (unnecessary interventions) must be met before the second (HRQOL) is formally tested. Since HRQOL may be influenced by earlier diagnosis from FET PET, the primary endpoint of unnecessary interventions should be met first to obtain a HRQOL result which is not caused solely by such a timing effect. This justifies a fixed-sequence testing approach—each tested at *p* = 0.05. If the first test is not significant, HRQOL results will be considered exploratory. The sample size was powered for the first endpoint, with a 10% increase to account for potential missing HRQOL data; a formal power calculation for HRQOL was not feasible due to limited prior data.

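### A wrong recurrence call that changes treatment can go uncounted in co-primary outcome 1, in either arm but probably more often with FET PET, because the final diagnosis has no unverifiable category

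*Protocol article*

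**What the plan says.** Four statements in the protocol article bear on this point.

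- **Event definition** (Primary study outcomes, co-primary outcome 1). The third of the four criteria for an unnecessary intervention is "Starting and/or altering chemotherapy for presumed tumor progression, in cases where the final diagnosis is pseudoprogression". The outcome is determined retrospectively by the researchers and the treating physician after 6 months of follow-up.
- **Reference standard** (same section). "The final diagnosis is based on clinicoradiological- and/or histopathological evidence". Tissue is therefore not required. Other study parameters lists the final diagnosis as tumour recurrence or pseudoprogression, with no third value.
- **Arm A management** (Intervention description {11a}). After a PET diagnosis of recurrence, "a change in treatment regime will be made". Redo-debulking is limited to clinical indications, so histology will not routinely check the call.
- **Usual MRI-only practice** (Background and rationale {6a}). When the MRI is uncertain, "the multidisciplinary team prefers to wait for a next scan", 6 to 12 weeks later. The same section describes pseudoprogression as mostly self-limiting.

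**The concern.** A wrong recurrence call sets off the treatment that then obscures the evidence against it. If the lesion was pseudoprogression it will tend to settle by itself, now under a new regimen, and the settling reads equally well as response. With only two values to choose from and no tissue, the recorded diagnosis will often stay at tumour. The patient is then scored as correctly treated.

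The opposite error is easier to see. If treatment is continued for presumed pseudoprogression and the lesion later grows, the second criterion records an event. An arm whose typical error is a wrong wait will have its errors counted more completely than an arm whose typical error is a wrong treatment change.

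Masked adjudication, or withholding the PET from the adjudicators, would not solve this, because the post-treatment course itself is ambiguous.

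Treating a tumour that is not there is a central harm of a false-positive PET. Co-primary outcome 1 also decides whether HRQOL is formally tested (Sample size {14}), and the Discussion links a positive trial to reimbursement. The secondary count of unnecessary treatment cycles depends on the same final diagnosis.

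**Working it through.** **1. The plan's own figure.** Inputs from Sample size {14}: 37% in the control arm, about 12% in the investigational arm, two-sided alpha 0.05, 90% power, Z test with pooled variance. The mean rate is (0.37 + 0.12)/2 = 0.245.

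n = [1.960 × √(2 × 0.245 × 0.755) + 1.2816 × √(0.37 × 0.63 + 0.12 × 0.88)]² / 0.25²
= [1.960 × 0.6082 + 1.2816 × 0.5820]² / 0.0625 = 60.1, so 61 per arm.

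This agrees with "we need 61 patients in each arm, so 122 in total". The sample-size arithmetic is not in question. The issue is what gets counted as an event.

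**2. How each treatment path is scored without histology.**

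| Path | Later course | Likely final diagnosis | Scored as event? |
|---|---|---|---|
| Treatment changed for presumed progression, lesion truly tumour | stable or smaller | tumour | no (correct) |
| Treatment changed for presumed progression, lesion truly pseudoprogression | stable or smaller | often tumour | often no (should be yes) |
| Temozolomide continued for presumed pseudoprogression, lesion truly tumour | growth | tumour | yes (correct) |

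The first two rows look the same at month 6. The article states no rule for separating them, and the two-value field forces a choice.

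**3. Effect of a net under-count when the arms are truly equal.** The article gives no PET error rate, no share of pseudoprogression in the trial population and no misclassification rate, so the size of the under-count is an assumption. Let m be the net under-count: points hidden in Arm A minus points hidden in Arm B. With 72 per arm, the recorded rates are p − m in Arm A and p in Arm B. The exact probability that the pooled Z test gives p<0.05 favouring PET is the sum of the binomial probabilities of all outcomes with z > 1.96.

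| Net under-count m | True rate 37% (protocol's control rate) | True rate 25% (assumed) |
|---|---|---|
| 0 points | 2.4% | 2.6% |
| 2 points | 4.2% | 4.8% |
| 4 points | 7.1% | 8.5% |
| 6 points | 11.3% | 14.1% |
| 8 points | 17.1% | 22.2% |

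**4. Effect on the planned result.** The planned rates give 0.37 × 72 = 26.6 and 0.12 × 72 = 8.6, so about 27 vs 9 events.

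- As recorded, 27 vs 9: pooled rate 36/144 = 0.250; SE = √(2 × 0.250 × 0.750/72) = 0.0722; difference 18/72 = 0.250; z = 3.46.
- With 8 uncounted Arm A events, 27 vs 17: pooled rate 44/144 = 0.306; SE = √(2 × 0.306 × 0.694/72) = 0.0768; difference 10/72 = 0.139; z = 1.81.
- With 7 (27 vs 16), z = 2.00. Eight is therefore the smallest number that removes significance, which is 8/72 = 11 points of the arm, with none hidden in Arm B.

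**The case against.** The strongest case on the other side has five parts.

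- **Arm B is not observed untreated.** The second criterion exists because temozolomide is continued during presumed pseudoprogression, bevacizumab may be given, and no concomitant care is prohibited. A reader might infer that waiting reveals the natural course. The article supports only that the lesion is seen without a change of treatment. This stands.
- **Waiting is not an Arm B rule.** It is a background statement about Dutch practice. Management is at the local board's discretion and the third criterion applies to both arms, so Arm B patients treated early for presumed progression meet the same problem. This stands, and it makes the bias a net difference.
- **Some wrong calls will surface.** Debulking for a clinical indication yields histology, and a pathological diagnosis of pseudoprogression is an event under the first criterion. Follow-up scans, dexamethasone dose and board notes are recorded and may lead to a revised diagnosis. This stands. A reader might infer that false-positive PET calls rarely become events, but no figure in the article supports that.
- **There are safeguards.** Equivocal PET results are managed as pseudoprogression, and rapid central review guides management. These should reduce the number of false-positive calls. They do not help to recognise the ones that remain.
- **The detail may sit in the full protocol or SAP.** Rules for the reference standard often do, and the missing-data section foresees sensitivity analyses where appropriate. This stands only in part. The two-value diagnosis is stated in the article itself, and a status not recorded at month 6 is hard to reconstruct later.

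**Conclusion.** The concern holds in a limited form. As defined, the endpoint can miss over-treatment that follows a wrong recurrence call. This is possible in both arms and probably more frequent in Arm A, so the likely direction is a net bias toward PET in co-primary outcome 1 and in the unnecessary-cycle count. That direction rests on two assumptions: that more Arm A than Arm B patients have treatment changed for presumed progression before the lesion has been followed, and that most of these have no histology.

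The size cannot be derived from the article. Net under-counts of 2 to 8 points give the probabilities in the working. A planned-size result would survive 7 uncounted Arm A events but not 8. A reader might go further and assume that every false positive in Arm A is hidden and none in Arm B. At an assumed 25% true rate, 12 hidden points would then give p<0.05 favouring PET 46% of the time. The documents do not support that as an estimate, because it needs full concealment in one arm, none in the other, and a true rate that they do not give.

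This should be addressed before month-6 diagnoses accumulate. It does not invalidate the main analysis.

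**What to change.** 1. In Primary study outcomes and Other study parameters, add a third status, not verifiable, to the final diagnosis. It applies in either arm to patients whose treatment was changed for presumed progression and who by month 6 have no histology, no later unequivocal growth and no tumour death. Growth is judged by one criterion, set in advance and the same for both arms.
2. Keep the main analysis as planned.
3. Report the number of not-verifiable patients by arm.
4. Pre-specify, for co-primary outcome 1 and for the cycle count, a tipping-point analysis that varies separately by arm the share of these patients reclassified as events.
5. Show the all-events and no-events cases only as outer bounds, and state that the all-events bound also counts true tumours that responded to treatment.

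Patient care is unchanged. The cost is one more category in the diagnosis field, one more judgement per affected patient at month 6, one sensitivity analysis and a wider stated range for the effect. Recruitment is expected to run until December 2027, so there is time to make the change.

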#### Secondary outcomes

Time-to-diagnosis (defined from the date of the index MRI result to the date of eventual management, including watchful waiting).Overall survival (defined from the date of the index MRI result to the date of death).Number of unnecessary treatment cycles during 6 months follow-up period (chemotherapy, bevacizumab).Cost-effectiveness, expressed in terms of incremental costs, incremental Quality-Adjusted Life Years (QALY), and Incremental Cost-Effectiveness Ratio (ICER). This is measured from a healthcare and societal perspective with use of three questionnaires: the iMTA Medical Consumption Questionnaire (iMCQ), the iMTA Productivity Cost Questionnaire (iPCQ), and EuroQol 5D-5L (EQ-5D) at *t* = 6 weeks, *t* = 12 weeks, and *t* = 6 months.HRQOL (continuous measure): EORTC-QLQ-C30 + BN20 at *t* = 6 weeks and *t* = 6 months (preferably before follow-up imaging is performed).PET characteristics as predictors of overall survival and progression-free survival outcomes.Determinants of unnecessary interventions.

#### Other study parameters

Patient characteristics: sex, age.Oncological characteristics: date of diagnosis of initial tumor, O^6^-methylguanine DNA methyltransferase (MGMT) promotor methylation status, CDKN2A/B-status, Karnofsky performance score at baseline and during clinical examination moments.Questionnaires EORTC-QLQ-C30 + BN20, EQ-5D, iPCQ and iMCQ at baseline, measured between informed consent and randomization.Diagnostic- and treatment characteristics: surgical- and concomitant chemoradiation characteristics, usage of bevacizumab, dosage of dexamethasone, follow-up scans, blood tests.Final diagnosis during follow-up after study intervention: tumor recurrence or pseudoprogression.Notes from multidisciplinary meetings, describing diagnostic uncertainty and initial management after diagnostic imaging.

The schedule of assessments is illustrated in Table 1.

**Table 1 Tab1:** Schedule of assessments

Visit	Index MRI result	Informed consent	Randomization	FET PET^a^	FET PET result^a^				
Study time	Day 1	± Days 3–14	±Days 5–16	± Days 7–30	± Days 10–33	Week 6	Week 12	Month 6	End of trial
Unnecessary interventions								X	
EORTC-QLQ-C30 + BN20/EQ-5D/iPCQ/iMCQ		X				X	X	X	
Karnofsky performance score	X				X^a^				
Final diagnosis								X	
Survival status								X	X^b^
Healthcare consumption								X	
Adverse events^c^				X	X				

^a^The intervention group only

^b^A survival sweep will be performed at the end of the trial

^c^All possibly/probably related adverse events will be reported for 30 days in both groups. All serious adverse events will be reported for 7 days in both groups

### Participant timeline {13}

Figure 2 shows the participant timeline.

**Fig. 2 Fig2:**
[figure not shown]
Participant timeline

### Sample size {14}

From current practice (survey among the participating centers), we estimate that 37% of the glioblastoma patients that meet our inclusion criteria, eventually undergo unnecessary interventions (control arm). In the intervention arm, we expect this proportion to be much lower (~ 12% from clinical scenarios), due to the high accuracy of [^18^F]FET PET. Using a two-sided *Z* test with pooled variance with an alpha of 0.05, based on a power of 90%, we need 61 patients in each arm, so 122 in total. Due to the intention-to-treat set-up and unnecessary treatment as outcome measure, we expect that virtually all patients can be included in final analysis, with minimal drop-out. For the co-primary endpoint of HRQOL (EORTC-QLQ-C30 + BN20) at *t* = 12 weeks, drop-out due to missing questionnaire data is estimated at 10%. With addition of this drop-out rate, we will randomize 144 patients, 72 patients per study arm.

Methodologically, the two primary endpoints are hierarchical: the first (unnecessary interventions) must be met before the second (HRQOL) is formally tested. Since HRQOL may be influenced by earlier diagnosis from FET PET, the primary endpoint of unnecessary interventions should be met first to obtain a HRQOL result which is not caused solely by such a timing effect. This justifies a fixed-sequence testing approach—each tested at *p* = 0.05. If the first test is not significant, HRQOL results will be considered exploratory. The sample size was powered for the first endpoint, with a 10% increase to account for potential missing HRQOL data; a formal power calculation for HRQOL was not feasible due to limited prior data.

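### Testing HRQOL only after endpoint 1 is met does not show that a week-12 HRQOL difference goes beyond earlier diagnosis, as the protocol says it does

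*Protocol article*

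**What the plan says.** The protocol article names two co-primary outcomes: any unnecessary intervention, and HRQOL at week 12. Under Sample size they are ordered, and HRQOL is formally tested only if the first is significant. The reason given starts from a concession: "Since HRQOL may be influenced by earlier diagnosis from FET PET". It continues that "the primary endpoint of unnecessary interventions should be met first to obtain a HRQOL result which is not caused solely by such a timing effect", and concludes: "This justifies a fixed-sequence testing approach—each tested at *p* = 0.05".

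Four other places bear on this:

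- **Statistical methods, primary parameters:** HRQOL at week 12 is compared between arms with Student's t test. The comparison has no term for diagnosis timing or for having had an unnecessary intervention.
- **Primary study outcomes:** endpoint 1 is determined retrospectively after 6 months of follow-up. One of its components is further chemotherapy given in the belief that the lesion is pseudoprogression when it finally proves to be progression. The HRQOL form is due at "12 weeks, preferably completed before follow-up imaging is performed".
- **Background and rationale:** Dutch teams faced with an uncertain MRI usually wait 6–12 weeks for the next scan, "leading to potential delay of diagnosis and adequate management and causing psychological burden for patients and their relatives with impact on quality of life".
- **Table 1:** the PET result is expected at about days 10–33, with the index MRI result as day 1.

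**The concern.** The protocol recognises two routes by which PET could change week-12 HRQOL: fewer unnecessary interventions, and earlier knowledge of the diagnosis. It then treats success on endpoint 1 as evidence that the second route is not the whole explanation. But endpoint 1 is a statement about intervention rates. A trial can truly reduce unnecessary interventions and also show an HRQOL difference that owes nothing to that reduction. A plain between-arm comparison cannot tell the two apart.

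HRQOL is a co-primary outcome, and the Discussion links a positive trial to reimbursement. If both tests are significant, the stated rationale would support reading the HRQOL result as more than an effect of earlier diagnosis. The design supports only a total effect of the strategy.

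**Working it through.** **1. The plan's own figure.** Inputs from Sample size: 37% versus 12%, and "two-sided *Z* test with pooled variance with an alpha of 0.05, based on a power of 90%, we need 61 patients in each arm". With a mean proportion of (0.37 + 0.12)/2 = 0.245:

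n = [1.960 × √(2 × 0.245 × 0.755) + 1.282 × √(0.37 × 0.63 + 0.12 × 0.88)]² / 0.25² = (1.192 + 0.746)² / 0.0625 ≈ 60.1, so 61 per arm.

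The figure reproduces. Power is 90.4% at 61 per arm and 94.5% at the 72 per arm to be randomised.

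**2. What passing the first test does to a timing-only HRQOL effect.** There were 20,000 simulated trials per scenario, with 72 per arm for endpoint 1 and 65 per arm for HRQOL (72 × 0.9 = 64.8, from the stated 10% missing questionnaires). The pooled Z test was followed by the t test. The document gives no HRQOL effect or SD, so the effect is an assumption, shown over a range. In the timing-only rows HRQOL does not depend on whether a patient had an unnecessary intervention.

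| Truth | First test passed | HRQOL significant, all trials | HRQOL significant, trials that pass |
|---|---|---|---|
| 37% v 12%, timing only, 0.2 SD | 95% | 20% | 20% |
| 37% v 12%, timing only, 0.3 SD | 95% | 40% | 40% |
| 37% v 12%, timing only, 0.5 SD | 95% | 81% | 81% |
| 37% v 12%, timing only, 0.7 SD | 95% | 98% | 98% |
| 37% v 37%, timing only, 0.5 SD | 5% | 81% | 80% |

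At 0.5 SD, both tests are significant in 0.95 × 0.81 ≈ 77% of trials, although no part of the HRQOL difference comes from avoided interventions. The last row shows what the sequence does achieve: if PET does not change interventions, a formal HRQOL claim is rarely reached (0.05 × 0.80 ≈ 4%).

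For comparison, suppose each unnecessary intervention costs 1 SD and there is no timing effect. The mean difference is then 0.25 × 1 = 0.25 SD, and HRQOL is significant in 26% of trials that pass. That lies between the 0.2 and 0.3 SD timing-only rows, so the test results alone do not identify the route.

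**3. Endpoint 1 is not independent of timing.** A control patient whose lesion is really progression, and who continues chemotherapy while waiting for the next scan, counts as having an unnecessary intervention. An earlier diagnosis can prevent that, so earlier diagnosis can help pass the first test. The document does not split the 37% by component, so this share cannot be sized.

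**4. The two endpoints cover different periods.** Endpoint 1 is determined after 6 months, and HRQOL is measured at week 12. An unnecessary intervention between those dates can contribute to endpoint 1 but cannot have affected the week-12 form.

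**5. Diagnostic status at week 12.** Counting from the index MRI result, week 12 is day 84. A PET result from day 10–33 is then 51–74 days old, about 7–11 weeks. For controls, two illustrations bound the position:

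- Next scans spread evenly over weeks 6–12 (assumption): share still waiting = 1 − (week − 6)/6, which is 100% at week 6, 50% at week 9 and 0% at week 12.
- All next scans at week 12, with the form completed first (assumption): 100% still waiting at both week 6 and week 12.

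So between 0% and 100% of controls may still be waiting when they complete the co-primary form. Because completion before imaging is only a preference, the protocol does not fix where in that range the trial falls.

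**The case against.** The strongest reply is that the sentence claims little. It says only that the result is not due to timing alone, and the sequence does stop a formal HRQOL claim when endpoint 1 fails. Fixed-sequence testing at 0.05 each also controls type I error. The primary objective compares management strategies, which is already a total effect, and the Discussion openly lists faster diagnosis among the expected mechanisms. All of this stands, and it limits the point to the stated rationale. It does not rescue that rationale: meeting endpoint 1 makes a second route possible but does not show that it contributed.

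Some stronger readings are tempting but not supported:

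- **That week 12 is where the timing effect is greatest.** No HRQOL data by time point are given. On the illustrations above, the contrast in diagnostic certainty is at least as large at week 6, a secondary time point.
- **That the timing effect outweighs the intervention effect by some number of points.** The document gives no per-patient effect for either route. Some PET results will be equivocal and some patients may not be scanned. An early diagnosis of recurrence could even lower HRQOL.
- **That month-6 HRQOL could serve as the test of benefit beyond timing.** Earlier diagnosis may act through earlier treatment, harms of interventions may have faded, and later forms are more exposed to death and non-response.
- **That the sponsor will overstate the result.** The analysis section commits only to statistical significance and clinical relevance between arms.

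The 6–12 weeks is also background on usual practice, not a trial scan schedule. It shows that the degree of timing effect is open, not what it is.

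**Conclusion.** The concern holds as a false stated property of the test on a co-primary outcome. When endpoint 1 is truly improved as planned, a timing-only HRQOL difference goes through unfiltered: about 95% of trials pass the first test, and the HRQOL significance rate is unchanged across assumed effects of 0.2 to 0.7 SD. That result rests on HRQOL being unrelated to unnecessary interventions in those scenarios, which is exactly the case the protocol says the sequence excludes. How much of a real week-12 difference would be timing cannot be derived from the document, and neither can its direction. An earlier-diagnosis effect may still be present at week 12, to an uncontrolled degree.

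A reader might infer that the fixed sequence is invalid or that the sample size is affected. Neither follows: the 61 per arm reproduces and the type I error control is sound.

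**What to change.** 1. Keep the fixed sequence, and justify it by type I error control and the priority of endpoint 1.
2. Delete the statement that meeting endpoint 1 first excludes an HRQOL result due to timing alone.
3. State that the week-12 contrast estimates the total effect of the PET-guided strategy, including earlier diagnosis, and that no benefit beyond timing will be claimed from it.
4. Derive from scan and questionnaire dates whether the follow-up scan preceded the week-12 form, and tabulate this by arm. Follow-up scans are already listed among the other study parameters.

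The cost is an amendment to the wording, one derived variable and a more modest HRQOL claim. Alpha, tests, sample size and visit schedule do not change. Recruitment is estimated to run to December 2027 and no interim analysis is planned, so the change can be made before the arms are formally compared.
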